### Design

The study design is shown in Figure 1. The STG arm will receive enhanced usual patient care plus a structured SMBG protocol at least quarterly. Patients in the ACG arm will visit their physicians quarterly and will continue their SMBG practice following their physician's recommendations. It is important to note that "usual care" in both groups involved more frequent clinic visits, point-of-care HbA1c tests, and free blood glucose meters and test strips; these additional services and resources are not generally available in most US primary care practices. Patients from both arms will be evaluated with the same scales and measures at the same time intervals over 12 months.

**Figure 1 F1:**
[figure not shown]
**Study design**.

### Procedure

STG participants will utilize the Accu-Chek^® ^360° View blood glucose analysis system (Tool) (Roche Diagnostics, Indianapolis, Indiana, USA). The system requires that patients record three consecutive day SMBG profiles. Each profile includes seven blood glucose tests/day (preprandial/postprandial at each meal and at bedtime), along with patient ratings of meal sizes and energy levels (see Figure 2). Space is provided to plot blood glucose results for better visualization of trends and patterns. Guidelines on the form indicate preprandial and postprandial blood glucose target ranges. The Tool also provides space for patients to note any comments or "learnings" relevant to their SMBG experiences. The Tool was designed to encourage collaborative discussion between patients and their physicians. Previous evaluations conducted with both patients and physicians have demonstrated that patients are willing and able to accurately complete the Tool [26] and that physicians are able to identify specific glucose patterns, determine the necessity for therapy change, and select specific pharmacological and lifestyle changes [26].

**Figure 2 F2:**
[figure not shown]
**Accu-Chek^® ^360° View blood glucose analysis system**.

Physicians and staff in the ACG and STG arms will be informed about the clinical investigational plan, including the rationale for the study, design of the study protocol, subject-related procedures, and use of evaluation questionnaires. Patients in both arms will receive a blood glucose meter (Accu-Chek^® ^Aviva blood glucose meter system, Roche Diagnostics, Indianapolis, Indiana, USA) and will be thoroughly trained in its operation. ACG patients will be instructed to use their meters following their physician's recommendations.

STG physicians and staff will receive training on interpreting the SMBG data provided by the Tool and will be provided with an algorithm that describes various pharmacologic/lifestyle treatment strategies that can be utilized in response to the specific SMBG patterns identified in their analysis of the Tool. STG physicians will be contacted regularly over the 12 months of the study to enhance the consistency of the intervention over time. All physicians will be blinded to all study-collected measures and scales. Point-of-care HbA1c equipment will be provided to all practices to ensure that any differential availability of this equipment does not affect outcomes.

STG clinic staff will conduct one-on-one training sessions with each STG patient to teach the SMBG protocol. This includes instruction in the use of the meter and administration of a DVD instructional program to explain and demonstrate how to complete the Tool, interpret the SMBG data, and make appropriate changes in lifestyle treatments. One-on-one discussions between patients and staff will provide an opportunity to review the content and purpose of the SMBG intervention, discuss what was learned from the DVD, enhance general understanding, personalize SMBG activities, and address questions and concerns.

Study duration will be 12 months, with patient visits occurring at initial screening and baseline, followed by completion of the Tool prior to visits at months 1, 3, 6, 9, and 12. The sequence of visits is described below and presented in Figure 3.

**Figure 3 F3:**
[figure not shown]
**Clinic visit schedule**.

#### Screening visit

After eligible patients have been identified via study protocol and contacted by mail, they will be invited to attend an initial screening visit at their physician's office. At screening, investigators will describe the study in detail, obtain written informed consent, record demographics, collect relevant medical history/lifestyle activities, perform physical examinations, collect laboratory samples, and document all current medications, including vitamins and supplements. Patients will also complete the STeP questionnaire, which assesses disease management behaviour, mood, quality of life, and diabetes-related self-efficacy, using validated self-report instruments.

#### Baseline visit

At the baseline visit, which will occur within 14 days of screening, clinic staff will provide all patients with a blood glucose meter and test strips, and patients will be instructed in the use of their blood glucose monitoring system. Laboratory results from the screening visit will be reviewed to ensure inclusion criteria have been met; if not, subjects will be discontinued from the study. Any changes in medications, vitamins, and supplements will be recorded. No diabetes-related treatment changes will occur during the baseline visit.

Staff will provide STG patients with the Tool and conduct one-on-one training with each patient. The instructional DVD program will be viewed and discussed. STG patients will be asked to complete the Tool and bring it to the month 1 visit. ACG patients will not receive the Tool or any additional SMBG training.

#### Clinic visits (months 1, 3, 6, 9, and 12)

At subsequent visits, ACG and STG clinic staff will collect laboratory samples and a point-of-care HbA1c test will be performed. Adverse events and changes in medications (including vitamins and supplements) will be recorded and a brief physical examination will be performed. Physicians will document missed work days, changes in medical history and lifestyle activities. In addition, patients in both groups will bring in their meter so that data can be uploaded electronically. They also will report any changes they have made to their diabetes regimen since they were last seen. ACG and STG patients will complete the STeP questionnaire (months 3, 6, 9, and 12), as well as a post-visit questionnaire at each visit to assess patient satisfaction with the visit and to record patient reports of any physician recommendations for pharmacologic and/or lifestyle changes that occurred during the visit. STG patients also will be asked if they brought their 360 View SMBG Tool to the visit and if their physician reviewed the form with them.

In reviewing the Tool, areas of needed regimen change will be identified and treatment changes based on this information will be made jointly. Depending on the treatment changes recommended, STG patients may be asked to complete an additional Tool within the next few weeks to evaluate the effectiveness of the new treatment changes and to determine if additional changes are warranted. In all cases, another Tool will be provided to the STG patients at the end of each visit, to be completed during the week preceding each patient's next quarterly visit. One week prior to their next scheduled office visit, STG patients will be prompted via telephone by their physician's office to complete the Tool.

### Measures

#### Primary Endpoint

The primary endpoint is glycaemic control, as assessed by change in HbA1c from baseline over 12 months. Blood samples will be collected at screening and the scheduled clinic visits (months 3, 6, 9, and 12). HbA1c analysis will be conducted by a central laboratory (Covance, Indianapolis, Indiana, USA). All scales and measures will contain patient codes rather than patient identifiers. Patient identifiers will be restricted to their physician's and to senior investigators.

#### Secondary Endpoints

##### Treatment Intensification

Treatment intensification includes two components. The first is pharmacologic modification, which is defined as the initiation of a new medication, the increase or decrease in the dose of an existing medication, or the termination of an existing medication. The second is recommended lifestyle modification, which is defined as any change in diet, exercise, or other management approaches. The total number of visits with recommended medication or lifestyle modifications and the time to the first treatment change will be recorded for all subjects.

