## Methods/Design

The Structured Testing Program (STeP) Study is a 12-month, cluster-randomised, multi-centre clinical trial to evaluate whether poorly controlled, non-insulin treated T2DM patients benefit from a comprehensive, integrated physician/patient intervention that uses structured SMBG. The study protocol was approved by the Copernicus Group (Central IRB) and is in compliance with the Helsinki Declaration [25].

The primary objective of the study is to determine if an integrated, intensive, and episodic SMBG intervention is associated with a significant reduction in HbA1c over 12 months, compared with enhanced usual care. The study will also examine group differences in: 1) timing and degree of treatment intensification; 2) changes in patient self-management behaviours over time; 3) changes in patient mood and quality of life (QOL) over time; and 4) cost effectiveness of the intervention.

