#### Additional Analyses (ITT and PP)

##### Mediator analyses

These analyses will examine whether critical variables, such as total number of visits, treatment intensification, physician recommendations for pharmacologic and/or lifestyle changes, frequency of Tool use, and changes in patient self-management behaviours (e.g., level of physical activity), mediated the effects of membership in each study arm on the primary and secondary outcomes over time.

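### The secondary endpoint named treatment intensification also counts dose decreases and terminations, so it measures treatment change in either direction and is not specific to intensification

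*Protocol article*

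**What the plan says.** In the protocol article, the Methods/Design section lists the "timing and degree of treatment intensification" first among the group differences to be examined beyond HbA1c, and the Abstract repeats it. The definition stands under Secondary Endpoints, Treatment Intensification: "Treatment intensification includes two components". One of them concerns drugs and opens with "pharmacologic modification, which is defined as the initiation of a new medication"; on the same footing, it goes on to count "the increase or decrease in the dose of an existing medication, or the termination of an existing medication". Lifestyle makes up the other component, which the section describes as "recommended lifestyle modification, which is defined as any change in diet, exercise, or other management approaches". Two measures are then named: "The total number of visits with recommended medication or lifestyle modifications and the time to the first treatment change will be recorded for all subjects".

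The Mediator analyses section lists, among the variables that may carry the effect of study arm to the outcomes, "total number of visits, treatment intensification, physician recommendations for pharmacologic and/or lifestyle changes". No section separates upward from downward changes.

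**The concern.** The objective and the endpoint's name promise a measure of therapy being stepped up, and of how soon and how far. The definition scores a dose cut or a stopped drug exactly as it scores an added drug or a dose increase. Either one ends the time to first change, and either one adds a visit to the count.

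This matters because the intervention is built to generate treatment changes. Under Procedure, only the structured testing group (STG) physicians are trained on the Tool and given an algorithm linking glucose patterns to treatment strategies. Under Clinic visits, the Tool review is meant to lead to joint regimen changes. Nothing in the text confines these to upward changes. An all-change endpoint may therefore show that the programme was followed without showing that therapy was intensified.

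The mediator analysis inherits the problem. A variable that pools upward and downward changes, which would be expected to act on HbA1c in opposite directions, cannot be read as the intensification pathway.

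**Working it through.** **1. Figure to reproduce.** The plan states no number for this endpoint. The check is one of definition, followed by an illustration.

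**2. Definition against objective.**

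| Type of change | Counts toward the endpoint? | Is it intensification? |
|---|---|---|
| Drug started | Yes | Yes, if glucose-lowering |
| Dose increased | Yes | Yes, if glucose-lowering |
| Dose decreased | Yes | No |
| Drug terminated | Yes | No, unless part of a switch |
| Any lifestyle change recommended | Yes | Direction not specified |

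**3. Summaries against objective.** Time to first change addresses timing, but of any change. The visit count says how often something was changed, not how far or in which direction. Neither recovers the degree of intensification.

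**4. Time to first change (all rates assumed).** Let *e* be the monthly rate of upward changes and *d* the monthly rate of other changes, constant and independent. The hazard of a first change is *e* + *d*, so the endpoint's hazard ratio, STG to active control group (ACG), is (e_STG + d_STG) / (e_ACG + d_ACG).

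*Dilution.* Take e = 0.10 in STG and 0.05 in ACG, a ratio of 2.0, with the same *d* in both arms:
- d = 0.02: 0.12 / 0.07 = 1.71
- d = 0.05: 0.15 / 0.10 = 1.50
- d = 0.10: 0.20 / 0.15 = 1.33

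*Apparent effect.* Take e = 0.05 in both arms, a ratio of 1.0, with d = 0.02 in ACG:
- d = 0.02 in STG: 0.07 / 0.07 = 1.00
- d = 0.03 in STG: 0.08 / 0.07 = 1.14
- d = 0.05 in STG: 0.10 / 0.07 = 1.43

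**5. Visit count (all means assumed, out of five visits, with changes at separate visits).**

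*Unequal downward changes.* STG has 1.0 upward and 1.0 downward; ACG has 1.5 upward and 0.2 downward.
- Protocol's count: 2.0 − 1.7 = +0.3
- Upward only: 1.0 − 1.5 = −0.5
- Upward minus downward: 0.0 − 1.3 = −1.3

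*Equal downward changes.* STG has 1.5 upward and 0.2 downward; ACG has 1.0 upward and 0.2 downward.
- Protocol's count: 1.7 − 1.2 = +0.5
- Upward only: 1.5 − 1.0 = +0.5
- Upward minus downward: 1.3 − 0.8 = +0.5

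Downward changes at equal rates pull the hazard ratio toward 1 but leave the difference in visit counts unchanged. An apparent effect, or a reversed sign, requires downward changes to differ between arms.

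**The case against.** The strongest defence is that the variable fits the trial's stated mechanism. The Hypothesis section expects benefit through starting and adjusting therapy as needed, and an all-change measure is a fair summary of that. The endpoint section itself uses neutral words for its components and summaries. A drug switch involves a termination without being a step down. Patients enter with HbA1c of 7.5 to 12.0%, so upward changes may well dominate. The endpoint is secondary and the mediator work is an additional analysis. All of this stands, and it supports keeping an all-change measure under a name that fits it. It does not make that measure one of intensification, which is what the objective and the mediator list call it.

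A reader might infer more than the document supports, in four ways:
- *That the endpoint fails to measure intensification at all.* It includes starts and dose increases. The fault is lack of specificity.
- *That vitamins and unrelated drugs count as events.* The endpoint section states no drug class, and under Clinic visits "changes in medications (including vitamins and supplements) will be recorded". But that passage describes general medication recording alongside adverse events and does not derive the endpoint. The full protocol, which is not shown, may set the class.
- *That the result will point the wrong way.* This needs a particular mix of changes by arm. Nothing in the document indicates that mix, and the 1.43 above assumes downward changes 2.5 times as frequent in STG as in ACG (0.05 / 0.02).
- *That differing numbers of attended visits would inflate the STG count.* Planned enrolment of 273 STG and 231 ACG patients for 204 completers each implies attrition of 1 − 204/273 = 25.3% and 1 − 204/231 = 11.7%. That would tend to lower the STG count, and whether to adjust for visits attended is a choice for the analysis plan.

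**Conclusion.** The point holds as a mismatch between a definition and the objective it serves. As written, the endpoint is a non-directional measure of treatment change, and it cannot by itself support a conclusion about the timing or degree of intensification. The mediator analysis carries the same ambiguity. This is stated in the article, so it is not a detail left to an analysis plan.

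The size cannot be determined from the document. The hazard ratios and visit counts in the working rest wholly on assumed rates. They show that dilution or an apparent effect is possible, not that either is likely. The primary HbA1c analysis and the sample size are untouched. The change should be made, but it does not threaten the trial's main conclusion.

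**What to change.** - Define pharmacologic intensification, for analysis, as starting a glucose-lowering drug or increasing its dose. Base time to first intensification, the visit count and the mediator variable on that definition.
- Report dose decreases and terminations separately, by arm.
- Keep the present composite, including lifestyle recommendations, as a further measure labelled *treatment change*. Physician recommendations already have their own place in the mediator list, so the lifestyle pathway is not lost.
- State in advance how a drug switch, one drug stopped and another started, is classified.

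The cost is endpoint wording and derivation code. The definition already names the types of change separately, so the work is classification, provided the records capture which type occurred. The price is fewer events in the narrower endpoint, hence less precision, and the need for the switch rule. Patient care and the primary analysis do not change.

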##### STeP Questionnaire

The STeP questionnaire incorporates the questions from standard psychometric instruments, as well as commonly used survey questions, to assess disease management behaviour, diabetes self-efficacy, well-being, depression, and diabetes-specific distress. Questions were drawn from the: 1) International Physical Activity Questionnaire (Short Form) [27]; 2) NCI Fruit & Vegetable Screener [28]: 3) National Cancer Institute (NCI) Percent Energy From Fat Screener [29]; 4) Hill-Bone Compliance to Medication Scale [30]; 5) Self-Monitoring of Blood Glucose (SMBG) [31]; 6) Treatment Self-Regulation Questionnaire (TSRQ) [32]; 7) Confidence in Diabetes Self-Care (CIDS-Type 2) [33]; 8) WHO-5 Well-Being Index (1998) [34]; 9) Diabetes Distress Scale (DDS) [35]; and 10) Patient Health Questionnaire 8 (PHQ-8) [36]. Clinic staff will be blinded from viewing these data.

##### Patient Post-Visit Survey

This survey records the subject's visit satisfaction and documents patient-reported treatment changes that were recommended by the physician during the visit. For STG patients, information on the usage of the Tool by both subject and physician will be collected.

##### Blood glucose meter data

SMBG data from both patient groups will be uploaded by the site coordinator directly to a web server at each study visit from the blood glucose meter via the Accu-Chek^® ^Smart Pix device (Roche Diagnostics, Indianapolis, Indiana, USA). Clinic staff will be blinded from viewing these data.

##### Clinical Data

Clinical laboratory evaluations will include hematolology, chemistry/immunology urinalysis, and point-of-care (HbA1c). Weight, height, blood pressure, pulse, respiration, and temperature will be recorded in the medical record and transcribed on the electronic record forms, where appropriate. A complete physical examination will be performed at screening and a brief physical examination will be performed at months 1, 3, 6, 9, and 12.

### Statistical analysis

In a cluster-randomised study, patients within a given cluster (in this case a clinical practice) often share many characteristics (e.g. ethnicity socioeconomic status, education level). Estimation of sample size, based on the assumption of the independence of individual observations, therefore may be inaccurate. Proper estimation of sample size for cluster-based studies requires estimates of the intra-class correlation coefficient (ICC) for each outcome variable of interest [37].

With change in HbA1c as the primary outcome variable, and using a two-sample t-test (two-sided, α = 0.05), a sample size of 204 per arm will have 90% power to detect a difference of at least 0.5% in change from baseline in HbA1c values, assuming a common standard deviation (SD) of 1.5%. The estimate of SD in HbA1c values was inflated from 1.15 to 1.50 due to the clustering effect [37,38].

#### Analysis of Dependent Variables

The analysis of change in HbA1c and other dependent variables (e.g. self-management behaviours) over time will be performed in two ways. First, the analysis will focus on the *intent-to-treat *(ITT) population, defined as all subjects who completed the baseline visit, regardless of their subsequent participation or compliance in the protocol over time. There will be no imputation of missing data values; however, a mechanism relevant to the missing data will be taken into account by using Linear Mixed Models (LMM) with SAS PROC MIXED, where it is assumed, initially, that the missing measurements of HbA1c are missing at random. Additional analyses of patient attrition at each step in the protocol from screening through the 12 month assessment also will be undertaken.

The second approach will be a *per protocol *(PP) analysis, which will compare ACG patients, STG patients who complied with the protocol, and STG patients who did not comply with the protocol. Compliance is defined as those STG patients who, at >4 clinic visits (out of a possible five visits), completed at least 80% of all blood glucose values on the Tool, brought their completed Tool to the clinic visit, and reported that their physicians looked at the Tool and discussed the results. This analysis will enable us to determine the effect of the SMBG intervention among those STG patients and physicians who participated fully in the program, compared to those who did not.

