**Discussion:**

The intervention and trial design builds upon previous research by emphasizing appropriate and collaborative use of SMBG by both patients and physicians. Utilization of per protocol and intent-to-treat analyses facilitates a comprehensive assessment of the intervention. Use of practice site cluster-randomisation reduces the potential for intervention contamination, and inclusion criteria (HbA1c ≥ 7.5%) reduces the possibility of floor effects. Inclusion of multiple dependent variables allows us to assess the broader impact of the intervention, including changes in patient and physician attitudes and behaviours.

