### Subjects

Thirty-four primary care practice sites in the eastern United States will be identified and recruited for participation in the study. The sites will include both small and large primary care practices, which serve communities with a range of patient education, social class, and ethnicity that reflects the diversity of primary care settings in the US. Each site will then be randomly assigned (cluster-randomised design) via a defined protocol to enhanced usual care (active control group [ACG]) or enhanced usual care with structured testing (structured testing group [STG]). Additional sites may be recruited as needed to ensure enough patients (minimum of 504 enrolled patients) to adequately power the study.

Two hundred thirty-one patients will be enrolled in the ACG, and 273 in the STG, which we estimate will lead to a total of 204 patients completing each arm at 12 months. Differential enrollment of practices and patients will be undertaken initially to account for potential differences in rates of attrition between the two study arms. Each practice will generate a list of all potential study patients who meet age, diagnosis, and HbA1c inclusion criteria from their individual databases or chart review. Participating physicians will review the list and eliminate any subject for medical reasons, as required by many human research committees in the US. Remaining patients will then be randomly selected from the list, using an external, study-defined protocol.

Inclusion criteria are: T2DM for greater than one year that is managed by their primary care physician; age 25 or more years; HbA1c ≥ 7.5-12.0%; treated by diet, exercise, oral diabetes medication, and/or injectable incretin mimetic; read and write English without assistance; and has not participated in any other research protocol within the last 30 days. Exclusion criteria are: T1DM; managed with insulin at the start of study; C-peptide level greater than 0.50 ng/mL; under the care of an endocrinologist or diabetologist; used systemic oral or inhaled steroids more than 14 days within last 3 months; treated with chemotherapy or radiation therapy; plans to relocate or travel extensively during next year; pregnant or breast feeding; and severe depression or other severe psychological conditions.

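### The per-protocol analysis claims the effect of the SMBG intervention from groups formed by compliance after allocation, in one arm only; randomisation protects neither contrast, and both can favour STG compliers when there is no effect.

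*Protocol article*

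**What the plan says.** Under Analysis of Dependent Variables, the Protocol article plans two analyses. The first is intent-to-treat, on everyone who completed the baseline visit. The second, per protocol, "will compare ACG patients, STG patients who complied with the protocol, and STG patients who did not comply with the protocol".

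An STG patient counts as compliant if three things happened at more than four of the five visits: at least 80% of the glucose values on the Tool were filled in, the Tool was brought along, and the patient reported that the physician looked at it and discussed it. As written, more than four of five means all five visits. ACG has no compliance criterion.

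The purpose is then given: "This analysis will enable us to determine the effect of the SMBG intervention among those STG patients and physicians who participated fully". The sentence ends by setting these patients against those who did not participate fully. The abstract adds: "Utilization of per protocol and intent-to-treat analyses facilitates a comprehensive assessment of the intervention". Additional Analyses carries both approaches into the mediator and moderator analyses.

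**The concern.** Practices were randomised, so all of STG can be compared with all of ACG. A subset of STG picked by later behaviour has no randomised counterpart. The rule selects patients who attend every visit and complete demanding paperwork, and physicians who review it. ACG keeps its dropouts and poor attenders. Because physician behaviour is part of the rule, compliers may also gather in better-functioning practices, which weakens the balance that practice-level randomisation was meant to give. Comparing compliers with non-compliers inside STG has the same defect.

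The article itself gives grounds to expect non-random selection: the Background section on protocol completion says that patient or disease characteristics may be linked to poor adherence. At stake is a causal statement about the intervention that selection alone could produce.

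**Working it through.** **1. The plan's own figure.** The article states that "a sample size of 204 per arm will have 90% power to detect a difference of at least 0.5% in change from baseline", with SD 1.5% and two-sided α of 0.05. A two-sample t-test with 204 per arm and standardised difference 0.5/1.5 has power 91.9%. Exactly 90% needs about 191 per arm. The stated figure is met with a small margin, and the point does not depend on it.

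**2. Inputs from the article.**
- Enrolment (Subjects): "Two hundred thirty-one patients will be enrolled in the ACG, and 273 in the STG", with 204 completers expected per arm. Implied attrition is 1 − 204/231 = 11.7% in ACG and 1 − 204/273 = 25.3% in STG. Under the all-five-visits rule, compliance could therefore not exceed about 204/273 = 75%.
- SD 1.5 (Statistical analysis).
- Compliant share p: 38.5%, 48% and 65%, the completion rates cited in the Background for three earlier trials, used here only as a range.

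**3. Assumption, not in the documents.** The correlation r between propensity to comply and HbA1c improvement in the absence of any effect: 0.1, 0.2, 0.3, with 0 as a check.

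**4. Formulas under no effect** (normal propensity, the top share p complies, z = Φ⁻¹(1 − p)):
- complier advantage over ACG = r × SD × φ(z)/p
- non-complier minus ACG = −r × SD × φ(z)/(1 − p)
- SE = SD × √(1/(273p) + 1/231), with 273p rounded
- rejection rate = Φ(−1.96 + bias/SE) + Φ(−1.96 − bias/SE)

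Example, p = 0.65 and r = 0.1: z = −0.385, φ(z) = 0.370, bias = 0.1 × 1.5 × 0.370/0.65 = 0.085. SE = 1.5 × √(1/177 + 1/231) = 0.150. Rejection rate 8.8%.

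| p | r | Complier advantage over ACG | Non-complier minus ACG | Complier minus non-complier | Rejection, complier vs ACG |
|---|---|---|---|---|---|
| 65% | 0.1 | 0.085 | −0.159 | 0.244 | 8.8% |
| 65% | 0.2 | 0.171 | −0.317 | 0.488 | 20.7% |
| 65% | 0.3 | 0.256 | −0.476 | 0.733 | 40.2% |
| 48% | 0.1 | 0.125 | −0.115 | 0.239 | 11.8% |
| 48% | 0.2 | 0.249 | −0.230 | 0.479 | 32.9% |
| 48% | 0.3 | 0.374 | −0.345 | 0.718 | 62.4% |
| 38.5% | 0.1 | 0.149 | −0.093 | 0.242 | 13.5% |
| 38.5% | 0.2 | 0.298 | −0.186 | 0.484 | 39.3% |
| 38.5% | 0.3 | 0.447 | −0.280 | 0.726 | 71.6% |

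HbA1c points; positive means more improvement in the first-named group.

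**5. Checks.** Simulation with 4,000 runs per setting agreed (for example 9.2% and 72.8% at the two extremes). With r = 0 the rejection rate stayed near 5%. The comparison of all STG with all ACG stayed near 5% in every setting.

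**6. Choice of SD.** The article says: "The estimate of SD in HbA1c values was inflated from 1.15 to 1.50 due to the clustering effect". If 1.15 is the patient-level SD, the bias shrinks by 1.15/1.5 = 0.77, to about 0.07 to 0.34 points. Keeping 1.5 in the SE to allow for clustering, the rejection rates become about 7% (0.066/0.150 = 0.44 standard errors) to 49% (0.343/0.177 = 1.94). The range is lower, but the conclusion is the same. Beyond this SD inflation, clustering is not modelled.

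**The case against.** **The sentence about effect may not refer to ACG.** It ends by contrasting full participants with those who did not participate fully, which may well mean STG non-compliers. This stands as a matter of reading, so one cannot say that the effect is claimed from complier versus ACG alone. It does not rescue the sentence: the within-STG contrast is equally non-randomised and has the larger bias in the table.

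**Non-compliers are shown, not dropped.** This stands and is a strength. Under pure selection they would fall below ACG while compliers rise above it, which gives readers a warning. The article does not say that the display will be used this way.

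**Intent-to-treat comes first.** This stands. A reader might infer that the per-protocol result is meant to replace a weak intent-to-treat result. The Background says only that intent-to-treat can potentially mislead when adherence is low and that later per-protocol analyses may then help. The sentence in the abstract says that both are used and is not in itself an error.

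**Direction and size are assumed.** This stands. A reader might infer that the analysis must favour STG. That requires compliance to go with better prognosis; with no such link the rejection rate stays at 5%.

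**Labelling and adjustment may be left to the analysis plan.** This is accepted, and their absence is not the point. The point is a causal claim that the article does make.

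**Conclusion.** The concern holds in limited form. The article attributes an intervention effect to a comparison of groups formed after allocation, and neither contrast on offer is protected by randomisation. For the assumed correlations of 0.1 to 0.3, compliance of 38.5% to 65% and SD 1.5, selection alone would give a complier advantage over ACG of about 0.09 to 0.45 HbA1c points, which is 17% to 89% of the 0.5 design difference. False-positive rates would be about 9% to 72%. These figures show what is possible and do not predict the bias in this trial.

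The documents do not support the stronger conclusion that the trial's main inference is compromised: the intent-to-treat comparison is unaffected. If the compliance rule was meant to read at least four visits, it would be looser but would still select on behaviour after allocation, so the conclusion does not rest on the all-five reading.

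**What to change.** - State that conclusions about the intervention's effect rest on the intent-to-treat comparison.
- Keep the three-group comparison, labelled descriptive and associational, and replace the sentence "This analysis will enable us to determine the effect of the SMBG intervention among those STG patients and physicians who participated fully" with one saying that the analysis describes outcomes by level of participation.
- When reporting it, compare STG non-compliers with ACG as a check for selection, and adjust for baseline HbA1c and practice clustering.
- Add a sensitivity comparison that applies the same visit-attendance criterion to ACG. This removes only the attendance part of the selection, because Tool completion and physician review have no ACG counterpart.
- Treat any complier-average estimate with arm as instrument as an optional sensitivity analysis, and state that its exclusion assumption is doubtful. Procedure gives STG physician training, a treatment algorithm and regular contact, and the Discussion says that the intervention goes beyond patients' use of the paper Tool.

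The cost is wording plus a little analysis on data already planned for collection. The downside is a weaker claim from the per-protocol analysis.
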